### Plans to give access to the full protocol, participant-level data and statistical code {31c}

The team plans to grant public access to the study protocol and de-identified data set after due request and commitment to adhere strictly to ethically consideration. This will only be available after 3 years of study completion.

## Oversight and monitoring

### Composition of the coordinating centre and trial steering committee {5d}

The team will constitute its own monitoring team to monitor the implementation of the project. Monitoring checklist will be developed for this exercise. Monitoring visits shall be carried out every 2 months or more frequently if indicated. The team shall hold review meetings with field supervisors weekly to check process, address challenges and motivate. The field supervisors shall submit weekly reports on activities of the field and shall be required to call if there is any emergency or disruptions in the field. The investigators shall hold team meetings monthly or more frequently, if necessary, to track the implementation process. A monitoring team shall be constituted from among the investigators to assess trial progress and safety of participants.

This study coordinating centre is the Epidemiology and Biostatistics Research Unit (EBRU), Institute for Advanced Medical Research and Training, College of Medicine, University of Ibadan. The institute comprises several research laboratories. Members of EBRU are diverse in expertise and are involved in various research projects including clinical/field trials and operational research. The investigators on the team to carry out this proposed study comprise of seasoned epidemiologists, seasoned primary healthcare specialist, nutrition expert, statistician, social scientist, cardiologist, policy experts, and a health economist.

The unit has been in existence for upward of 10 years and are well experienced in clinical/field trials and operational /implementation research. These include studies on home management of malaria, intermittent preventive treatment (IPT) use in pregnancy, artemisinin combination therapy (ACT) effectiveness and feasibility studies, intervention to improve ITN use among under-fives and pregnant women, neglected tropical diseases—helminthiasis, hypertension in adults and children, salt intake and hypertension among school children and other community-based studies. The team has carried out many of their research works in collaboration with the Federal Ministry of Health and State Ministries of Health.

The College of Medicine has an IT unit that supports researchers on issues related to technology and M-health. It has the REDCAP software that will support this project in kind with data capturing. The unit shall provide advice and purchase the Cloud system, the SMS messaging App to be used for the IT component of this study from the grant money to be provided by TETFund.

### Composition of the data monitoring committee, its role and reporting structure {21a}

A data monitoring committee was not considered as this was a low-risk intervention.

### Adverse event reporting and harms {22}

The interventions are mostly behavioural. Therefore, no serious adverse event is anticipated. However, any adverse event due to use of antihypertensive medications will be addressed as routinely done in clinics.

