### Intervention description {11a}

The highlights of the activities and assessments for intervention and control arm are shown in Table 1. The components of the intervention include the following.

**Table 1 Tab1:** Highlights of the activities and assessments for intervention and control arm

	Activity	Intervention	Control
1	Baseline survey	Yes	Yes
2	Selection, screening and standard training of CORPs on blood pressure screening	Yes	Yes
3	Training on additional information on follow-up care for hypertensive patients and CORPs coordination	Yes	No
4	Trained CORPs screen and refer community members found to have high blood pressure	Yes Referral to the designated primary healthcare centre in the community	Yes Referral will be to the community member’s health facility of choice
5	Train health facility staff in designated primary healthcare facilities on the National guideline for hypertension treatment	Yes	No
6	CORPs Monthly checking and recording of blood pressure as well as providing health education/counselling support by the CORPs	Yes	No
7	SMS messaging on medication and healthy lifestyle adherence to support follow-up care	Yes	No
8	Anthropometry measurement, e.g. weight, height and body mass index (BMI) Biochemical measurement ECG	Yes	No
9	Endline survey	Yes	Yes

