#### iv. Community-based hypertension follow-up care by CORPs

The CORPs will conduct routine follow-up patients in their homes monthly checking their blood pressure, adherence to medication and providing health education/counselling support. In addition, the CORPs will ask about their attendance to health facility as they were scheduled/advised and sought reasons for non-attendance among those who may not have adhered. The CORP will organize group lifestyle education session weekly where experiences will be shared and patients will engage in group exercises among other relevant activities. Follow-up record form will be used by CORPs to detail information on patients’ compliance with drug, the health education provided and BP measurements. A CORP will be attached to 20 hypertensive patients for follow-up care. The intervention will be for 6 months.

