### Outcomes {12}

The Primary outcomes are (i) change in baseline proportion of patients with controlled blood pressure, (ii) the mean change in blood pressure at 6 months between patients in the intervention and control communities. The secondary outcome measures are (i) change from baseline in proportion of patients adhering to medication, (ii) change in proportion of patients who are overweight/obese, smoke, take alcohol, practice unhealthy dietary habit and are physically inactive. In addition are (iii) mean improvement in quality-of-life score, (iv) percentage increase in satisfaction with care score, (v) change in awareness, knowledge, perception and practice, (vi) proportion of CORPs assessed to have good competency score, (vii) perception about quality and acceptability of home-based follow-up care delivered by CORPs, (viii) incidence of cardiovascular events among patients, (ix) change in baseline proportion of patients assessed to have high cardiovascular risk, (x) mean cost of treatment of hypertension, (xi) mean change in lipid level, urinary sodium and food sodium content. These variables will be measured at the end of the second, fourth and sixth month follow-up period.

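### Cardiovascular-event incidence is a secondary outcome, but follow-up contact between enrolment and endline is scheduled in the intervention arm only, so the comparison is open to differential detection

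*Protocol article*

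**What the plan says.** **Outcome and timing.** Outcomes {12} names "incidence of cardiovascular events among patients" as secondary outcome (viii). The same section closes: "These variables will be measured at the end of the second, fourth and sixth month follow-up period". No arm is specified.

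**Contact in the intervention arm.**
- Table 1, under Intervention description {11a}, row 6: "CORPs Monthly checking and recording of blood pressure as well as providing health education/counselling support by the CORPs", marked Yes for intervention and No for control.
- Row 8 (anthropometry, biochemistry, ECG) is also Yes for intervention and No for control.
- The section on initial treatment sets clinic appointments at one month and every two months after that, for patients in the intervention sites.
- Trial design {8} places the 6-month follow-up study in the intervention arm.
- The form used at home visits records drug compliance, "the health education provided and BP measurements".

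**Contact in the control arm.** After screening and referral to a facility of the person's own choice, Table 1 lists only the endline survey (row 9). Under Eligibility criteria {10}, people who are unwell when a survey takes place are excluded from it.

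**Withdrawal.** Section {11b} lets an intervention patient who develops a complication be withdrawn after case review. It states no counterpart for controls.

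**Safety.** Adverse event reporting and harms {22} says "Therefore, no serious adverse event is anticipated" and that "any adverse event due to use of antihypertensive medications will be addressed as routinely done in clinics". Section {5d} states: "A monitoring team shall be constituted from among the investigators to assess trial progress and safety of participants".

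**The concern.** An incidence comparison is fair only if an event has about the same chance of being recorded in each arm. Here one arm is seen at home every month and in a designated clinic at set intervals, while the other has no listed study contact for six months. A stroke or admission among intervention patients is likely to come to the study's notice. The same event in a control patient, treated at any facility, may not. The one assessment listed for both arms at the end of follow-up excludes those too ill to take part and cannot interview those who have died, so it is weakest for the patients who had events.

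If the plan is followed as written, outcome (viii) mixes risk with intensity of observation. The investigators intend to advocate scale-up if the package works. Event counts by arm would then be read as evidence on benefit or harm, and the monitoring team charged with participant safety would review counts gathered unequally.

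**Working it through.** The article states no event rate, capture rate or expected count for outcome (viii), so there is no figure to reproduce. The check has two parts.

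**1. Is there a control-arm contact that could deliver months 2, 4 and 6?**

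| Time | Intervention arm | Control arm |
|---|---|---|
| Months 1 to 6 | monthly home visit (Table 1, row 6) | none listed |
| Month 1, then every 2 months | clinic appointment | none listed |
| Baseline and end | ECG and biochemistry (Table 1, row 8) | No in Table 1; the ECG and specimen sections name no arm |
| Endline | survey (row 9) | survey (row 9) |

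Months 2 and 4 have no control-arm activity behind them. At month 6 the only contact common to both arms in Table 1 is the endline survey.

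**2. What could unequal capture do?**

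Inputs:
- 300 patients per arm. Sample size {14} gives 50 per arm in each LGA, and there are six LGAs: 50 × 6 = 300, or 600 in all.
- Assumed, not in the article: 6-month risk of 2%, equal in both arms; capture of 95% in the intervention arm and 90%, 70% or 50% in controls.

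Recorded events = 300 × risk × capture. Observed risk ratio = true risk ratio × (capture in intervention ÷ capture in control).

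Intervention arm: 300 × 0.02 × 0.95 = 5.7 recorded events.

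| Control capture | Control events recorded | Observed ratio if truth is 1.0 | Observed ratio if truth is 0.70 |
|---|---|---|---|
| 90% | 300 × 0.02 × 0.90 = 5.4 | 0.95/0.90 = 1.06 | 0.74 |
| 70% | 300 × 0.02 × 0.70 = 4.2 | 0.95/0.70 = 1.36 | 0.95 |
| 50% | 300 × 0.02 × 0.50 = 3.0 | 0.95/0.50 = 1.90 | 1.33 |

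The ratio does not depend on the assumed risk; only the counts do. At 1% risk they are 2.85 against 2.7, 2.1 or 1.5. At 5% they are 14.25 against 13.5, 10.5 or 7.5.

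**Direction.** Withdrawal under {11b} works the other way if events after withdrawal are not counted. If a share w of the intervention arm's otherwise captured events is lost in this way, the ratio is multiplied by (1 − w). The two effects cancel when w = 1 − (control capture ÷ 0.95): 5% for control capture of 90%, 26% for 70% and 47% for 50%. With a larger w, the error favours the intervention. The article fixes neither quantity, so the sign of the net error is unknown.

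**The case against.** **Both arms are said to be followed.** The abstract describes follow-up of patients in both arms over six months, the schedule in Outcomes {12} names no arm, and the sections on ECG and on specimens carry no arm restriction. It would therefore be too strong to say that controls have no study contact at all. The narrower statement stands: Table 1 lists nothing for controls between enrolment and endline, and its row 8 disagrees with the ECG and specimen sections.

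**Forms and definitions may sit elsewhere.** Confidentiality {27} mentions case record forms and medical records, and {18a} promises operating procedures for each data collection activity. The questionnaire sections listed in the article describe the survey, not every trial form. The absence of an event form or event definition from an article is therefore no finding. The point rests on the unequal contact that the article states.

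**Stronger readings that the text does not support.**
- A reader might infer from {22} that drug reactions stay outside the trial's records. The sentence concerns how drug-related events are handled clinically. It does not say that they go unrecorded.
- A reader might see a contradiction between expecting no serious adverse event and counting cardiovascular events. The first concerns harm from a mostly behavioural package, the second the underlying disease. They can coexist.
- A reader might assume much poorer capture in controls and claim a large spurious excess under the intervention. Nothing in the article supports a particular capture rate, and the withdrawal provision leaves the direction open.
- A reader might fault the plan for making no safety outcome of urea and creatinine. They may serve clinical or risk assessment, so this is a preference and not an error.

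**Importance.** Outcome (viii) is one of eleven secondary outcomes, and the primary outcomes are blood pressure control and mean change. With the small counts illustrated, it would be imprecise even with equal detection. This limits the weight of the point but does not remove it.

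**Conclusion.** The point holds in a limited form. As scheduled in this article, the between-arm comparison of cardiovascular events is open to differential detection: follow-up contact is set out for the intervention arm alone, the shared endline survey excludes people who are unwell, and the withdrawal provision for complications applies to one arm. This is more than missing detail, because following the stated activities produces the imbalance.

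Its size cannot be derived from the article. Under assumed capture of 95% against 50-90%, a null effect would appear as a ratio of 1.06 to 1.90, and a true ratio of 0.70 as 0.74 to 1.33, before any loss of events through withdrawal. The net direction is unsettled. The primary outcomes are outside this point. The change is worth making because it is cheap and because event counts by arm are likely to be cited if the package is put forward for scale-up.

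**What to change.** 1. Reconcile the schedule in Outcomes {12} with Table 1. Either give both arms the event enquiry at months 2, 4 and 6, or state that the between-arm comparison of outcome (viii) is made at 6 months only.
2. Base that comparison on one identical enquiry in all recruited patients of both arms, covering death, hospital admission, and stroke or cardiac event. At minimum this is a single 6-month recall at the endline contact. Use a household informant when the patient has died or is too ill to answer, so that the survey's exclusion of unwell people does not apply to this enquiry.
3. Make the enquiry independently of the home visits, include patients withdrawn under {11b}, and check reports against medical records where these are available.
4. Report events found only through home visits separately and leave them out of the between-arm comparison.
5. Send the results by arm to the monitoring team of {5d}.
6. Reconcile Table 1 row 8 with the ECG and specimen sections, so that it is clear whether controls have these measurements.

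The minimum version costs a few more questions at endline, some tracing of informants and some recall error. Extra calls at months 2 and 4 would improve recall but would add study contact to a usual-care arm, so they are optional.

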### Frequency and plans for auditing trial conduct {23}

The study steering committee will meet every month to review the trial progress and address any implementation challenges as they arise.

### Plans for communicating important protocol amendments to relevant parties (e.g. trial participants, ethical committees) {25}

The ethical review committee has a standing guideline as to how to apply for amendment in a protocol. This will be followed if the need should arise. The grant supporting body, Tertiary Education Trust Fund (TETFund), National Research Fund (NRF), shall be notified through a letter and the approved amended protocol after the ethical committee has approved the amendment. The study participants will be informed duly as the amendment affects their participation. This may be done at individual or group level. Trial registries shall be notified using the registry’s guideline.

### Dissemination plans {31a}

We would make our results available to the community of scientists with interest in this field in order to prevent unintentional duplication of the project. We would welcome collaboration with other implementing partners who could make use of information obtained from our project for formulation of policies. We shall disseminate by doing the following:

## Dissemination to the local authorities

The findings of this cluster-randomized controlled trial shall be presented and communicated in the appropriate local governments in each state to key stakeholders in the community, local government as well as the States Ministry of Health and the Federal Ministry of Health. In addition, the group shall on an annual basis organize a 1-day hypertension awareness programme during which risk factors for hypertension and preventive measures shall be discussed.

## Dissemination to policy makers

So also, our findings will be presented relevant key stakeholders in the States Ministry of Health and the Federal Ministry of Health. This will be useful in formulating appropriate policy in line with the scale up of response to non-communicable diseases (NCD) in Nigeria. They will be encouraged to engage with relevant bodies and implementing partners providing CVD-related programmes.

## Dissemination to the scientific community

We will present and discuss our findings at the institutional, national, continental and international scientific meetings. The group will publish newsletter annually. The newsletter’s intent is to disseminate new information from our research. The activities and discoveries of the project will be allocated 40% of the newsletter’s coverage. In addition, the group will also create a website where information about project as well as the diseases of interest shall be posted regularly. The language shall be made simple and short and the primary audience is the general public.

## Discussion

This study is one of the few ongoing studies targeting hypertension control in Nigeria with the intention of involving community in the management through ownership of intervention process that will foster sustainability. It is a multi-centre study including three states representing the three major ethnicities in Nigeria, the Hausa, Igbo and Yoruba. The study is based on community-clinical linkage using task sharing concept of healthcare delivery in underserved urban and rural communities. Nigeria, a low-resource setting, is characterized by shortage of physicians and health workers in urban and especially rural areas [43]. Task sharing and task shifting is defined as the allotment of tasks usually performed by highly trained healthcare workers (doctors and nurses) to less specialized health workers, who often have less education and training [44, 45]. It has been demonstrated that patients can effectively be assessed for CVD risk and managed in primary care facilities by non-physician health workers in low-resource settings [46]. An adequately trained local workforce with the capacity to initiate and sustain CVD prevention and management programmes would be a good complement to formal healthcare delivery system. In this study, we seek to develop a team of local healthcare human resource to provide sustainable CVD prevention and hypertension follow-up care in the community. The intervention package to be deployed will focus on improving knowledge of hypertension, early diagnosis of hypertension and identification of those with risk factors of cardiovascular diseases, promoting healthy lifestyle for reduction of CVD risk factors in the community.

The study will be one of the first few studies in Nigeria that will be evaluating the effectiveness of training community-oriented resource persons to screen for hypertension and provide health education services on the clinical outcomes of hypertensive patients comparing the intervention and control arm. This will be achieved by health education and awareness campaign, task sharing using the community-oriented resource persons (CORPs) in the community for home-based follow-up care and building health facility human and infrastructure capacity.

The high prevalence of hypertension and the increasing trend of early onset is a major concern in the development of a nation as the young and active workforce population are being incapacitated and worst still depleted. The Nigerian government in a bid to combat poverty, hunger, disease, illiteracy, environmental degradation and discrimination against women adopted the United Nations sustainable development goals (SDGs), which are interdependent and influence health and vice versa [47]. However, efforts in the various sectors including poverty reduction (SDG 1) have not yielded the desired results or outcome and have stalled the achievement of other SDGs. This proposed study addresses achieving good health and well-being, which is goal 3 of the SDGs. It stands to provide evidence-based information for the adoption of an effective strategy in the control of hypertension with the goal of reducing mortality and morbidity as well as improving the workforce for nation development. The study will also empower the communities to take ownership of the intervention for sustainability of the project.

The study is not without limitation. This study is coming up in a pandemic era and could be disrupted at some points in the implementation. These include possibility of delay in commencement, health facility attention to the project may be distracted and patients’ adherence may be hindered. The team shall endeavour adherence to all the COVID-19 preventive measures. The CORPs and health facilities will be provided with face masks and hand wash and sanitizers. Field activities will be suspended should there be a lockdown till when eased.

Basing the status of blood pressure on readings on one single visit during survey may not show the true prevalence of hypertension in the communities with likelihood of overestimation. However, using an average of three BP measurements with resting periods in between is expected to minimize this.

The population characteristics of the urban and rural areas could differ especially with age and sex bearing in mind population migration factors and dynamics. This may distort the true effect of the intervention on outcome as CVD risk factors varies in these groups of people. This will be adjusted at analysis using multilevel analysis with random effect model. Bias in the intervention study will be minimized by randomization. The possible contamination between control and intervention arm will be reduced by grouping/clustering the communities before randomization and ensuring buffer zones exist between them to limit diffusion.

Cluster-randomized design is appropriate for this study which by nature is evaluating the effectiveness of an interventions in a “real-world setting” [48], and meant to provide health education at both community and individual levels. In addition is the fact that it is also an effective way to avoid contamination. The limitations associated with its use such as prevention of interference shall be giving much attention at analysis.

In conclusion, this study stands to provide evidence-based information for scaling up task sharing as well as community-clinical linkage in the control of hypertension in Nigeria. It is expected that this intervention will bring about early detection of hypertension, reduction in mean blood pressure and an increase in the proportion of patients with controlled blood pressure. In addition, we expect an improvement in the mean quality of life score; healthy lifestyle and competent CORPs as well as the reduced mean cost of treatment of hypertension in the intervention arm of the study. All of these will inform policy review to guide the control of hypertension and reduction in cardiovascular diseases risk in Nigeria.

